#### Exercise capacity tests

To assess functional exercise capacity of the upper extremity, the 30-s arm curl test will be used according to the guidelines in the Senior Fitness Test Manual [28]. Participants will be instructed to sit on a chair with their back straight and feet flat on the floor. For women, a dumbbell weighing 5 lb. (2.3 kg) is used, and for men one weighing 8 lb. (3.6 kg). The weight will be held in the dominant hand, perpendicular to the floor. Participants will be instructed to move from the down position to the curled-up position without wrist movement. On the signal “go,” participants are to curl as many times as possible in 30 s.

To assess functional exercise capacity of the lower limb extremity, the 6MWT will be conducted following the ATS guidelines [29]. A 30-m straight line will be selected, and a chair placed at each end to signify the beginning and end of the testing area. Patients will be instructed to walk back and forth as quickly as possible over 6 min. At the start and end of the test, a modified Borg CR10 test will be used to assess the exercise intensity and dyspnea by the patients themselves. The test will be performed twice with a 30-min rest. After the test, the longest distance will be recorded and used for analysis.

#### Questionnaires

The questionnaires mainly assess quality of life, physical activity, and self-efficacy.

Health-related quality of life will be assessed by St. George’s Respiratory Questionnaire [30], which consists of three domains: symptoms (cough, sputum, asthma attack, etc.), activity (climbing, dressing, housework, etc.), and impact (anxiety, distress, insecurity, etc.). Scores range from 0 to 100, with higher scores reflecting a poorer quality of life.

Physical activity will be assessed by the Physical Activity Scale for the Elderly. The questionnaire asks about the physical activities performed in the last 7 days, and contains three domains: recreational physical activity, domestic physical activity, and occupational physical activity [31]. Questions are weighted and quantified at different levels, and higher scores reflect a higher level of physical activity.

Self-efficacy will be assessed by the Chronic Disease Self-Efficacy Scale, a six-item scale assessing confidence when performing certain activities. Higher scores indicate higher self-efficacy.

### Statistical analysis

SPSS version 23.0 will be used for data management and statistical analysis. A Kolmogorov–Smirnov test will be used to test for normality, and the normality data will be expressed as mean ± standard deviation, while skewed data will be expressed as median and interquartile range. An intention-to-treat analysis will be used for the allocation, irrespective of whether the participant completes the intervention. Missing outcome data will be handled using a mixed-model method. Then a per-protocol analysis will be conducted, which will include only subjects who completed all outcome measures and followed the intervention protocol. Comparisons of baseline differences between groups will be performed using one-way analysis of variance (ANOVA) or a non-parametric test. Training-related effects will be assessed using 2 × 2 ANOVA (group × time). Differences between variables over time (time effect, from baseline to 3 months) in each group will be evaluated using a paired *t*-test or a non-parametric test. For categorical variables, a chi-squared test will be employed to detect differences. A two-tailed *P* value of <0.05 will be considered to be significant. In addition, differing intervention effects on pulmonary function have been found in previous studies [4, 32, 33], and disease severity may be an important contributor. Therefore, a pre-specified subgroup analysis will be performed to investigate the differences in effectiveness according to disease severity.

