### Adherence

For patients in the CG, compliance will be quantified by the number of responses to telephone calls conducted once a week by the specialist, with compliance defined as no less than 85%. In other words, there should be no fewer than 11 responses. For patients in the three intervention groups, compliance will be quantified by the completion of the exercise log by patients and attendance at the supervised training sessions in the hospital. Compliance will be defined as no less than 85% of exercise sessions completed.

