### Outcome measurement

All participants will undergo assessments within 1 week of being enrolled at baseline and at the end of 3 months. The primary outcomes are the pulmonary function test, 30-s arm curl test, and 6MWT. Secondary outcome measures include the Modified Medical Research Council Dyspnea Scale (mMRC), dual-energy X-ray absorptiometry (DXA), respiratory muscle strength test, peripheral skeletal muscle strength, sEMG, and questionnaires.

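### The per-protocol set requires every outcome measure to be complete, so an adherent patient with valid 6MWT values can be dropped from the per-protocol 6MWT comparison because an unrelated test is missing

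*Protocol article*

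**What the plan says.** The Statistical analysis section sets out two analyses in order. The first is by allocation: "An intention-to-treat analysis will be used for the allocation, irrespective of whether the participant completes the intervention". It is followed by "Missing outcome data will be handled using a mixed-model method". The second is a per-protocol analysis, which will "include only subjects who completed all outcome measures and followed the intervention protocol". The two conditions are joined, and completeness is not limited to the primary outcomes or to the outcome being analysed.

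The Outcome measurement section shows how wide the completeness condition is. "The primary outcomes are the pulmonary function test, 30-s arm curl test, and 6MWT". The secondary list starts with the mMRC and DXA and continues with "respiratory muscle strength test, peripheral skeletal muscle strength, sEMG, and questionnaires". The Questionnaires section describes three instruments: SGRQ, PASE and the self-efficacy scale. Participants undergo "assessments within 1 week of being enrolled at baseline and at the end of 3 months".

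Following the intervention has its own definition in the Adherence section. For the exercise groups: "Compliance will be defined as no less than 85% of exercise sessions completed". For the control group, compliance is measured by responses to weekly telephone calls, with the same 85% threshold.

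**The concern.** A per-protocol analysis is meant to show the effect among those who followed the protocol. The compliance rule in the Adherence section already identifies them. Requiring all measures to be complete adds a second filter that has nothing to do with adherence. A patient who did the exercise and walked at both visits is removed from the per-protocol 6MWT comparison because, say, an sEMG recording or a questionnaire is missing.

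Two things are at stake. The per-protocol comparison loses precision for no gain. A difference between the intention-to-treat and per-protocol results also becomes harder to interpret, because it could reflect who completed the test battery and not who adhered.

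**Working it through.** **Count of measures.** Three primary (pulmonary function, arm curl, 6MWT), five secondary tests (mMRC, DXA, respiratory muscle strength, peripheral muscle strength, sEMG) and three questionnaires: 3 + 5 + 3 = 11. A patient without a 6MWT cannot enter a 6MWT comparison of patients with observed data under any rule. The cost of the all-measures condition for the 6MWT therefore comes from the other 11 − 1 = 10 measures.

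**Inputs from the Sample size section.** Difference 54 m, SD 57 m, two-sided alpha 5%, power 80%, 18 evaluable per group.

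**The plan's own figure.** n per group = 2 × [57 × (1.960 + 0.842) / 54]² = 17.49, rounded up to 18. This agrees with the protocol. At 18 per group, power is 81% by the normal approximation and 79% (78.8%) by the t-test. The t-test is used below, with df = 2n − 2 and noncentrality 54 / (57 × √(2/n)). At n = 18 the noncentrality is 2.84.

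**Assumptions.** The documents give no rate of missing tests, so two patterns are shown. Both start from 18 per group who have the 6MWT, before any removal for non-adherence. Fractional n is an expected count.

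*Clustered gaps:* a share q of patients has at least one of the other measures missing. n = 18 × (1 − q).

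| q (assumed) | n per group | t-test power |
|---|---|---|
| 5% | 17.1 | 77% |
| 10% | 16.2 | 74% |
| 20% | 14.4 | 69% |

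*Independent gaps:* each of the 10 other measures is missing with probability m, independently. Share kept = (1 − m)^10; n = 18 × share kept.

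| m (assumed) | share kept | n per group | t-test power |
|---|---|---|---|
| 1% | 90% | 16.3 | 74% |
| 2% | 82% | 14.7 | 70% |
| 3% | 74% | 13.3 | 65% |
| 5% | 60% | 10.8 | 55% |

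**With an outcome-by-outcome set.** A missing secondary test removes nobody from the 6MWT comparison. The 18 per group and 79% power are kept at this step, and only non-adherence reduces them further.

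**The case against.** The strongest reply is that little hangs on this analysis. The intention-to-treat analysis comes first, with a mixed model for missing outcomes, and a patient with a valid 6MWT and a missing sEMG stays in it. That stands. A reader might infer that the rule throws primary-outcome data out of the trial's main comparison; the Statistical analysis section does not support that.

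A reader might also infer that the rule tilts the set towards fitter patients, since the maximal-effort tests are hard for people with severe disease. This is plausible, because the trial enrols stages II to IV, but no section gives missingness by severity. Exclusion criteria 4 to 6 already screen out patients whose condition hampers strength testing, prevents sEMG or contraindicates body composition assessment. Deterioration after entry and the respiratory pressure tests are not covered, so selection remains possible but undocumented. The compliance filter may itself favour fitter patients, and the proposed change keeps it.

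The independent-gaps table can be challenged too. If gaps arise because some patients are too ill or tired, they fall in the same people and multiplication overstates the loss. A wholly missed visit loses all measures together; that belongs to the 20% drop-out allowance, and no redefinition recovers it. This is fair, and it is why the clustered case is shown beside the independent one.

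Two smaller replies remain. A single completer-and-adherer set gives one denominator throughout, which is a real but modest convenience. The phrase may also be an article's shorthand for attending both assessments. That reading is possible, but the published sentence states a rule, and followed literally it has the effect described.

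**Conclusion.** The point holds for the supportive per-protocol analysis only. As stated, the rule excludes adherent patients from the per-protocol 6MWT comparison for reasons unrelated to adherence or to the 6MWT. The same applies to every other outcome analysed in that set.

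The size is modest if gaps cluster: about 2 patients per group and 5 percentage points of power (79% to 74%) when 10% of patients have a gap. It grows to about 7 patients per group and 24 points (79% to 55%) if each of 10 measures is missing independently in 5%. Both ends rest on assumed rates.

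These power figures measure lost precision. A reader might take them to mean that the trial misses its design power, but the 80% in the Sample size section was not claimed for the per-protocol set.

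**What to change.** Replace the per-protocol sentence in the Statistical analysis section. For each outcome, the per-protocol set should consist of participants who meet the compliance rule in the Adherence section and have that outcome at baseline and at 3 months. Remove the condition that all outcome measures be complete, and report the per-protocol denominator for each outcome.

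The cost is one sentence, plus denominators that differ slightly between outcomes and must be shown in the tables. The Trial status section says recruitment is under way, so the change can be made and dated before outcome data are analysed.

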**Methods/design:**

This study is a single-blind, randomized controlled trial. A random number table will be generated by an independent person. Each number will be placed in a sealed opaque envelop to blind assignment. All outcome assessors will be blinded to group assignment.

COPD patients between 40 and 80 years of age, with stable medical treatment and no regular participation in regular exercise in the last 6 months will be included. All participants will be recruited from the Respiratory Medicine Department of Yue-Yang Integrative Medicine Hospital Affiliated to Shanghai University of Traditional Chinese Medicine.

All participants will continue to follow their medical treatment. They will be randomly assigned to one of four groups in a 1:1:1:1 ratio: (1) usual care (control group, CG), (2) pulmonary exercise group (PG), (3) resistance exercise group (RG), or (4) combined pulmonary exercise and resistance exercise group (PRG). CG participants will receive medical treatment only. PG participants will perform 60 min of exercise twice a day 7 days a week for 3 months, with 1 day’s exercise per week at hospital under guidance and supervision. RG participants will perform 60 min of resistance exercise once a day, three times a week for 3 months, with 1 day’s exercise per week at hospital under guidance and supervision. PRG participants will perform 60 min of prescribed pulmonary exercise combined with resistance exercise for 3 months.

The outcomes include the isokinetic strength of peripheral skeletal muscle, surface electromyography, 6-min walking distance, 30-s arm curl test, pulmonary function, respiratory muscle strength, dyspnea, body composition, physical activity, quality of life, and Chronic Disease Self-Efficacy Scale.

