Hence, in this study, 3 months of (1) usual care, (2) prescribed pulmonary exercise, (3) exercising with resistance bands, and (4) prescribed pulmonary exercise combined with exercising with elastic bands will be applied as interventions to COPD patients to evaluate the overall effect of prescribed pulmonary exercise on lung function, exercise capacity, skeletal muscle function, quality of life, and psychological function in patients with COPD. The aim of the study is to further clarify the role of prescribed pulmonary exercise in COPD rehabilitation, since it is a simple, fun, easy to learn, operational, and effective intervention for COPD patients. We hypothesize that prescribed pulmonary exercise can significantly improve pulmonary function, exercise capacity, skeletal muscle function, quality of life, and psychological function, and that combined exercise induces additional benefits in COPD patients compared with single exercise methods.

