There are several highlights to this study. First, the prescribed pulmonary exercise is a rearrangement of traditional Chinese exercise and targeted to COPD patients. The effects of this prescribed pulmonary exercise on lung function, respiratory muscle strength, exercise capacity, skeletal muscle function, quality of life, and physical activity on stable COPD patients will be evaluated. Second, the role of prescribed pulmonary exercise in improving skeletal muscle function and exercise capacity will be determined by comparing the effects of pulmonary exercise and an elastic band program. Third, the effect of pulmonary exercise combined with exercising with elastic bands in stable COPD patients will be determined, and the effects compared with a single program to determine whether combined exercise can achieve additional beneficial effects. Fourth, the study will apply comprehensive measurements to evaluate skeletal muscle function in patients with COPD, including isokinetic muscle strength testing, surface myoelectricity, 6MWT, and the 30-s arm curl test. Fifth, a sub-analysis will be performed to investigate if the treatment effects differ in patients with different disease severity to enable the optimization of treatment effects for all patients suffering from the troublesome disease. Finally, the study is in strict accordance with CONSORT guidelines, so that the effects of the prescribed pulmonary exercise can be clearly determined.

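### The stated 2 × 2 (group × time) ANOVA does not match a four-arm trial measured at two times, and leaves open which arms are compared and at what error rate

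*Protocol article*

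**What the plan says.** The abstract's Methods/design paragraph gives the allocation: "They will be randomly assigned to one of four groups in a 1:1:1:1 ratio". The arms are CG, PG, RG and PRG, and the Design section repeats them. Outcome measurement sets two assessments: "All participants will undergo assessments within 1 week of being enrolled at baseline and at the end of 3 months".

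For continuous outcomes, Statistical analysis names one test of the intervention effect: "Training-related effects will be assessed using 2 × 2 ANOVA (group × time"). The same paragraph compares the groups at baseline by one-way ANOVA or a non-parametric test. It assesses change over time separately, where differences "in each group will be evaluated using a paired *t*-test or a non-parametric test". It declares an intention-to-treat analysis and adds: "Missing outcome data will be handled using a mixed-model method". Significance is a two-tailed P below 0.05, and no adjustment is mentioned.

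The comparisons of interest are spread over the article. Sample size is built on PG versus CG. The hypothesis at the end of the Background is that "combined exercise induces additional benefits in COPD patients compared with single exercise methods", that is, PRG versus PG and PRG versus RG; the Discussion repeats this aim. The Discussion also says that the role of pulmonary exercise "will be determined by comparing the effects of pulmonary exercise and an elastic band program", that is, PG versus RG.

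**The concern.** A 2 × 2 group × time ANOVA has room for two groups, and this trial has four. The sentence is the only between-arm test that the article gives for continuous outcomes, which include all three primary outcomes (pulmonary function, 30-s arm curl, 6-min walk). As written it does not say which two arms enter, whether the analysis is repeated for each pair, or whether arms are pooled.

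Two things are at stake. The choice of comparison is left to the analyst, possibly after the data have been seen. And if the 2 × 2 is repeated over pairs, each at 0.05, the chance of at least one false positive on an outcome is well above 5%.

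**Working it through.** **Inputs from the protocol article.** Four arms, 1:1:1:1 (abstract, Design); two assessment times (Outcome measurement); two-sided alpha 0.05 (Sample size, Statistical analysis); difference 54 m, SD 57 m, power 80%, 18 per group (Sample size).

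**1. The plan's own figure.** For one two-group comparison, n per group = 2 × (1.960 + 0.842)² × 57² / 54² = 2 × 7.85 × 1.114 = 17.5, so 18. The stated 18 is reproduced. Power at 18 is 0.811 by the normal approximation and 0.788 by the t distribution. The size is thus that of a single contrast, PG versus CG.

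**2. Degrees of freedom of the interaction.**
- Design as randomised: (4 − 1) × (2 − 1) = 3.
- Model as stated: (2 − 1) × (2 − 1) = 1.

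A single 2 × 2 therefore carries one of the three independent arm contrasts.

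**3. What a 2 × 2 on one pair does.** With two times, its interaction is equivalent to a two-sample t-test on change from baseline. It is a valid between-group test of that pair.

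**4. Repeating it over pairs.** Four arms give 4 × 3 / 2 = 6 pairs.
- If the six tests were independent: 1 − 0.95⁶ = 0.265.
- The pairs share arms, so the tests are correlated. Simulation with no true arm difference (20,000 runs, 18 per arm, SD 57 m, assumed baseline-to-3-month correlation 0.5, 0.7 or 0.9, common change of 0 or 20 m) gives at least one P < 0.05 in 0.200 to 0.207 of trials. The correlation and the 20 m are assumptions, and the result hardly depends on them.
- In the same runs the 3-df group × time test rejects in 0.049 to 0.051.
- For the four contrasts that the article sets out, the independence figure is 1 − 0.95⁴ = 0.185.

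These rates are per outcome.

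**5. Price of adjusting.** For a 54 m difference at 18 per arm:

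| Bonferroni over | n per arm for 80% (normal) | Power at 18, normal | Power at 18, t |
|---|---|---|---|
| 3 contrasts | 24 | 0.67 | 0.63 |
| 6 pairs | 27 | 0.58 | 0.52 |

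**The case against.** The strongest reply is that this is a slip for 4 × 2. The baseline comparison in the same paragraph uses a one-way ANOVA, which takes four groups, so the authors knew how many there were. That may well be so, but the printed model is still wrong and an analyst following it has to guess. A second reply is that the 2 × 2 could mean a factorial (pulmonary exercise yes/no by resistance exercise yes/no). The article's own label for the two factors, group and time, rules that out. A third is that contrasts and multiplicity are often left to a fuller document. That stands as far as mere silence goes; the point here is that the model which is stated does not fit the design.

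Several stronger readings are tempting, and the article does not support them:

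- *That the stated contrasts cannot be tested.* Each one is between two arms, and a 2 × 2 on that pair tests it. What fails is a single 2 × 2 for all of them.
- *That conclusions about arms would rest on the within-group paired tests.* The article assigns training effects to the group × time analysis and uses paired tests only for the time effect within each group.
- *That the ANOVA is a completers' analysis labelled intention-to-treat.* A conventional repeated-measures ANOVA would drop participants without a 3-month value, but the article also promises a mixed-model method for missing outcomes. Exclusion is one reading of loose wording, not something stated.
- *That pairwise models lose important precision through a smaller error term.* The trial was sized for a two-group comparison, so no planned power is lost.

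**Conclusion.** The point holds in limited form. The only stated between-arm test of continuous outcomes is a two-group model in a four-arm trial: 1 interaction degree of freedom where the design has 3. That mismatch follows from the text alone and needs no assumption.

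The consequence is ambiguity over which arms are compared. If the ambiguity is resolved by running all six pairs at the stated 0.05, familywise error is about 0.20 per outcome. That figure assumes normally distributed changes with equal variance and no true arm difference. It is conditional on the pairwise reading, which the article neither states nor excludes. If the sentence is a slip for 4 × 2, the overall test keeps its 5% level, but the wording still needs correcting, and the choice and error control of the pairwise contrasts would still have to be settled.

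**What to change.** Replace the sentence with one linear mixed model per continuous outcome: group (four levels), time (two levels) and group × time, including all randomised participants. This also brings the effect test into line with the intention-to-treat and mixed-model sentences beside it.

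Take PG versus CG, on which the sample size rests, as the main contrast at 3 months. Follow it with PRG versus PG, PRG versus RG and PG versus RG, either in a stated order or with a multiplicity adjustment, each with a 95% confidence interval. Base conclusions about arms on these between-group estimates, and call the within-group paired tests descriptive.

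The cost is wording. The software already named (SPSS 23) fits the model, no new data are needed, and the article reports the trial as still recruiting. If PG versus CG comes first at 0.05, it keeps its planned power. The downside falls on the secondary contrasts: with Bonferroni over the remaining three, power for a 54 m difference at 18 per arm is about 0.67 (normal) or 0.63 (t), before counting any condition that PG versus CG be significant first.

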### Sample size

The sample size was based on detecting a minimum difference of 54 m in the 6MWT [11] between the control group (CG) and the pulmonary exercise group (PG) and used a baseline standard deviation of 57 m [11]. With a power of 80% and an alpha of 5% (two-sided), the minimum sample size per group is 18 to give a total of 72 participants. Assuming a drop-out rate of 20%, the minimum sample size in total is 88 (22 participants in each group). The participants will be recruited to achieve a balanced number of patients with different levels of severity of COPD.

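### The planned group × time test compares change scores but the trial was sized on a baseline SD; the power statement therefore assumes an unstated correlation of about 0.5, and baseline adjustment would be more efficient

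*Protocol article*

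**What the plan says.** Three statements in the protocol article bear on this.

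- **Test.** Under Statistical analysis: "Training-related effects will be assessed using 2 × 2 ANOVA (group × time"). No baseline covariate is named. A mixed model is mentioned there, but only as the way to handle missing outcome data.
- **Visits.** Under Outcome measurement: "All participants will undergo assessments within 1 week of being enrolled at baseline and at the end of 3 months". There are thus two time points.
- **Sizing.** Under Sample size: "The sample size was based on detecting a minimum difference of 54 m in the 6MWT". The comparison meant is usual care (CG) against pulmonary exercise (PG). The calculation "used a baseline standard deviation of 57 m". Its error rates are given as follows: "With a power of 80% and an alpha of 5% (two-sided"). The article's result is that "the minimum sample size per group is 18 to give a total of 72 participants". Losses are then allowed for: "Assuming a drop-out rate of 20%, the minimum sample size in total is 88 (22 participants in each group").

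The article gives neither an SD of change nor a correlation between baseline and 3-month values.

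**The concern.** With two visits and two arms, the group × time interaction is algebraically the difference between arms in mean change, so its test is the two-sample t-test on change scores. The variance that governs it is that of the change, which depends on how strongly a patient's two measurements are correlated. The trial was sized on the spread of single measurements between patients, which contains no such correlation. The power statement and the planned test therefore rest on different variances, and they coincide at only one value of ρ.

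A second, related matter is efficiency. Every participant has a baseline value, but the planned contrast subtracts it in full instead of weighting it by how well it predicts the 3-month value. With about 18 to 22 patients per arm, that choice affects precision and how chance baseline imbalance feeds into the estimate.

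**Working it through.** **Inputs.** From the Sample size section: difference 54 m, SD 57 m, two-sided 5%, power 80%, 18 per arm before drop-out. ρ is not given, so it is an assumption and is shown over a range. The SD is taken as 57 m at both visits. The comparison is CG versus PG on the 6-min walk.

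**1. The plan's own figure.** n per arm = 2 × [57 × (1.960 + 0.842)/54]² = 17.49, rounded up to 18. The stated size reproduces by the normal approximation (noncentral t gives 19). Power at 18 per arm with SD 57 is 81.1% (normal) or 78.8% (noncentral t).

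**2. SD behind each analysis.**

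- Change score (planned test): 57√(2(1−ρ)). This equals 57 only when 2(1−ρ) = 1, that is ρ = 0.5.
- Adjusted for baseline: 57√(1−ρ²).
- Variance ratio, adjusted to change: (1−ρ²)/(2(1−ρ)) = (1+ρ)/2, which is below 1 for every ρ below 1. That is 35% less variance at ρ = 0.3, 25% less at 0.5 and 15% less at 0.7.

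**3. Power at 18 per arm.** The noncentrality for the change score is 54/(SD × √(2/18)); at ρ = 0.3 it is 54/(67.4 × 0.333) = 2.40 on 34 degrees of freedom, giving 65%. The adjusted column allows for the lost degree of freedom (33 left) and for the variance added by chance baseline imbalance.

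| ρ (assumed) | SD of change, m | Change-score power | Adjusted SD, m | Baseline-adjusted power |
|---|---|---|---|---|
| 0 | 80.6 | 50% | 57.0 | 78% |
| 0.2 | 72.1 | 59% | 55.8 | 79% |
| 0.3 | 67.4 | 65% | 54.4 | 81% |
| 0.4 | 62.4 | 71% | 52.2 | 84% |
| 0.5 | 57.0 | 79% | 49.4 | 88% |
| 0.7 | 44.2 | 95% | 40.7 | 97% |

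A simulation of 100,000 trials per value at ρ = 0, 0.2, 0.3, 0.5 and 0.7 agrees: 50%, 59%, 65%, 79% and 94% for change scores, and 78%, 79%, 81%, 88% and 97% with adjustment.

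**4. Break-even.** Setting 17.49 × 2(1−ρ) = 18 gives ρ = 0.485 for 80% power (normal approximation). If all 22 per arm were retained it would fall to about 0.37 (0.40 by t), but the planned 20% drop-out leaves 22 × 0.8 = 17.6, about 18.

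**5. Chance imbalance.** The standard error of the baseline difference between two arms of 18 is 57√(2/18) = 19 m. At ρ = 0.5, an imbalance of that size moves the change-score contrast by (1−0.5) × 19 = 9.5 m, against a target of 54 m. Baseline adjustment corrects for this in expectation.

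**The case against.** **No shortfall is shown.** This stands. A reader might infer from the low-ρ rows that the trial is underpowered. The article does not support that: it gives no ρ, and from about 0.5 upward the planned test meets or exceeds its stated power. Nothing in the article shows that ρ is low. Some features may point the other way: the walk test is done twice and the longer distance kept, patients must be clinically stable, and GOLD stages II to IV and ages 40 to 80 give a wide spread between patients. These do not establish a value either.

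**The planned test is valid.** This also stands. Under randomisation the change-score contrast is unbiased; the case for adjustment is precision.

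**Adjustment does not make power independent of ρ, and it is not strictly free.** Correct. Adjusted power still runs from about 78% to 97% over ρ = 0 to 0.7, and it is just under 80% at ρ = 0 to 0.2. At ρ = 0 it is about one point below a t-test on follow-up values alone (77.6% against 78.8%). It nonetheless exceeds the planned change-score test at every ρ in the table.

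**The mixed model may already cover this.** Only in part. It is named for missing data, and an ordinary group × time mixed model without a constraint on baseline means gives the same change-score contrast among completers.

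**There are four arms.** The t-test identity holds for a pairwise comparison, not for an omnibus four-group interaction. The sizing is for one pair, so the identity applies where the power claim is made.

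**Covariates are often left to a fuller plan.** True, and a missing covariate list would be no finding. Here the article itself names the test and the planning SD, and those two do not match.

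**Conclusion.** The point holds as a mismatch between two stated choices and as an available gain in precision. The sizing arithmetic before drop-out is sound for a comparison with SD 57 m, but the planned test has that SD only at ρ = 0.5. The power statement therefore carries an unstated assumption that ρ is about 0.5 or more. Whether power is lost cannot be determined from the article.

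The gain from adjustment depends on ρ: about 16 percentage points of power at 0.3, 9 at 0.5 and 2 at 0.7. The variance reduction is a fraction (1−ρ)/2 at any ρ, before the small covariate cost. These figures assume equal SDs at both visits and 18 analysed per arm, and they concern the CG–PG walk-distance comparison only, the single comparison that was sized. The algebra is certain; the practical consequence is conditional.

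**What to change.** Replace the unadjusted group × time contrast, as the main between-group analysis, with one of these:

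- the 3-month value compared between arms with the baseline value of the same outcome as covariate (ANCOVA); or
- a mixed model with both visits as responses and baseline means constrained equal across arms, which also keeps participants who lack a 3-month value.

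Restate the power for that analysis, giving the assumed ρ and its basis, or a range such as the one above.

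Baseline FEV1 %predicted may be added as a further covariate but is optional. It is not in the figures above, and it is redundant where FEV1 is itself the outcome.

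The cost is one degree of freedom and a change of analysis wording. Baseline values are already scheduled, so no patients, visits or measurements are added. The Trial status section describes the trial as recruiting; on that status the change can be specified before the outcome data are analysed.
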